### 2.5. Procedures 

The trial will be conducted within the context of a three-week in-hospital multidisciplinary rehabilitation program for weight loss based on nutritional, physical, and psychological rehabilitation [50,51,52], according to the Italian National Health System recommendations. As part of the nutritional program, adolescents will be assessed by a staff dietician and placed on an individualized hypocaloric diet composed of 53% carbohydrates, 26% fat, and 21% protein [53] and a fluid intake of at least 1500 mL per day^−1^. They will also follow a daily nutritional counseling program provided both in individual and group settings, comprising dietetics lessons. As for physical rehabilitation, young patients will participate in a physical activity program consisting of five group training sessions per week lasting about 45–60 min per day of physical therapy comprising aerobic activities such as walking and cycling under the supervision of a therapist. The physical program also entails 2 h per week of aerobic leisure activities. As far as the psychological component is concerned, patients will take part in psychological counseling sessions that are provided at least once a week lasting about one hour each, carried out by a clinical psychologist, and aimed at promoting a healthy lifestyle and addressing psychological factors related to the onset of dysfunctional lifestyle habits. 

At week 1 of the hospitalization, all the patients will be screened for admission to the study with a clinical interview conducted by a clinical psychologist blinded to research aims to provide information about the study and assess the eligibility criteria according to the Diagnostic and Statistical Manual of Mental Disorders (DSM-5). Weight and height, to calculate BMI, will be measured by the internal medical team. Once we obtain informed consent to participate from parents and written assent from participants, young patients recruited for the study will be randomly assigned into two conditions. The experimental group will attend TAU plus a brief ACT-based intervention that comprises three sessions, provided once a week, lasting about one hour each, while the control group will attend TAU only. 

At pre (Time 0/week 1) and post-psychological intervention (Time 1/week 3), patients of both conditions will be invited to fill the questionnaires under the supervision of a member of the research team. 

In case of any form of psychological discomfort due to the participation in the intervention or any doubt or need for information concerning the trial, participants will have the opportunity to consult the psychologist responsible for the study. Once enrolled, patients can withdraw from the study at any time. This will not affect their future treatment. 

The clinical psychologist who will conduct the sessions, participants, and observers will be blinded to research aims. 

Completed questionnaires will be stored in a room used for research in the hospital, which is accessible only for research team members. Data will be stored on password-protected files kept for five years after the end of the trial. 

The study protocol was approved by the Ethical Committee of the Istituto Auxologico Italiano (registration number 2021_01_26_03) and registered on ClinicalTrials.gov (last update on 7 June 2021). All procedures will be conducted following the Helsinki Declaration and its later advancements.

The schedule of enrolment, intervention, and assessment in the study is presented in Figure 1 (see also Supplementary Materials). 

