### 2.3. Measures

All demographical (gender, age, nationality, educational level, and family composition) and clinical data will be collected via self-report using Italian validated and widely used questionnaires. The following psychological measures will be collected pre (Time 0/week 1) and post (Time 1/week 3) psychological intervention. 

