### 2.9. Statistical Analysis 

Descriptive statistical analyses will be conducted to investigate the baseline characteristics of the sample. To evaluate differences between the two groups (ACT + TAU vs. TAU only) across the two time points (pre—Time 0/week 1; post—Time 1/week 3 psychological intervention), repeated measure between groups ANOVAs will be performed for each dependent variable—namely, AFQ-Y, PWB, DASS-21, DERS, and DEBQ. In this case, a global effect size (Cohen’s f and/or eta-squared—η^2^) will be used to quantify the [global] difference of the two groups across times. Global effects size will be interpreted with the following benchmarks [63]: null (*f* < 0.10; η^2^ < 0.003); small (f from 0.10 to 0.25; η^2^ from 0.003 to 0.039); moderate (*f* from 0.25 to 0.40; η^2^ from 0.40 to 0.110); and large (*f* ≥ 0.40; η^2^ > 0.110). Moreover, several focused comparisons will be performed to assess differences both within and between groups. In particular, differences between the two groups will be assessed using an independent samples t-test both at the baseline as well as at the end of psychological treatment, separately—namely, T1: ACT + TAU vs. TAU and T2: ACT + TAU vs. TAU. Conversely, differences within each group across the two time points will be assessed using dependent samples t-test—namely, ACT + TAU: T1 vs. T2; and TAU: T1 vs. T2. The magnitude of the differences will be interpreted by using the Cohen’s d [64]—more in detail, for between-groups comparisons, the classical Cohen’s d formula will be used; in contrast, for within-groups comparisons, the modified formula for dependent data will be used. Each Cohen’s d will be interpreted using the following benchmarks: null (*d* < 0.20), small (d from 0.20 to 0.49), moderate (d from 0.50 to 0.79), and strong (*d* > 0.80). 

Participants who reported missing data as well as subjects who will not participate in each therapy session will be excluded from the final sample, and thus, their data will not be analyzed. Moreover, also, participants who drop out from the program will be excluded from the final sample. 

Analyses will be carried out using Jamovi (version 1.6.15) [64].

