## Figures and Tables

**Figure 1 ijerph-18-06225-f001:**
[figure not shown]
Spirit figure.

**Table 1 ijerph-18-06225-t001:** The ACT-based intervention.

Session Number	Domains	Goals and Therapeutic Processes	Experiential Activities and Metaphors
Session 1 Week 1	Openness	The purpose of this session is to develop the willingness to experiencing distress and undesirable private events as part of human experience, without judgment or attempts to avoid or control internal states, even if they are unpleasant.	Experiential exercise: “How would my life be if…” In this experiential activity, young patients are guided to answer the key question: “How would my life be if I didn’t have … [my problem that I have]”. The problem could be their weight or anything else related to their condition of obesity or any other perceived problem in their life. Participants are encouraged to describe what they desire to do if they did not have obesity, in order to take distance, observe and accept their conditions and related thoughts and feelings.
Session 2 Week 2	Awareness	The purpose of this session is to promote the ability to be present at the moment and face events as contextually situated. To be aware means stepping back from suffering situations and seeing them in the context where they occur.	Metaphor: “The sky and weather metaphor” [58]. In this metaphor, personal thoughts and feelings are presented as the weather and the self as the sky. The weather naturally changes. Despite that, it can never harm or change the sky. No matter how bad the weather, the sky always has room for it. Sometimes, we forget that the sky is there, but it is still there. In the same way, difficult thoughts and feelings can occur. No matter how harmful they are, the self is still there. We can always learn how to access this part of us. It is a safe space that contains difficult thought and feelings.
Session 3 Week 3	Engagement	The purpose of this session is to foster values clarification and engagement in actions linked to personal values, such as relationships and personal growth. If a person engages himself in committed actions driven by chosen life directions, they can pursue a meaningful and coherent life.	Experiential exercise: “The treasure hunt”. In this experiential exercise, young patients are asked to draw a treasure hunt in which the treasure is a value in their life and the route is made of behaviors that need to be engaged to reach a meaningful life.

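### The exclusions in Section 2.9 remove adolescents who stop ACT because of distress, so the DASS-21 and DERS comparisons cover completers only and can understate worsening under ACT

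*Protocol article*

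**What the plan says.** Section 2.5 anticipates discomfort from taking part ("In case of any form of psychological discomfort due to the participation in the intervention") and offers support: "participants will have the opportunity to consult the psychologist responsible for the study". It also allows free withdrawal: "Once enrolled, patients can withdraw from the study at any time".

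Section 2.3 schedules all psychological measures at two points, "pre (Time 0/week 1) and post (Time 1/week 3) psychological intervention". Section 2.3.2 lists the DASS-21 (depression, anxiety, stress) and the DERS (emotion regulation) as secondary outcomes. Under Section 2.5, both arms are invited to complete the questionnaires at both times, with a research team member supervising.

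Section 2.9 compares each scale between arms by 2 × 2 repeated-measures ANOVA and by t-tests. It then restricts who is analysed. Participants with missing data are excluded. So are those who miss a session: "subjects who will not participate in each therapy session will be excluded from the final sample, and thus, their data will not be analyzed". Dropouts are treated in the same way: "participants who drop out from the program will be excluded from the final sample".

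**The concern.** The likely behavioural result of discomfort with a psychological intervention is that the adolescent skips the next session or leaves. Those are two of the events that trigger exclusion in Section 2.9. The rule therefore selects on a possible consequence of treatment, and it does so mainly in one arm, because TAU participants have no ACT session to miss.

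The DASS-21 is the trial's direct measure of distress in participants aged 12 to 17. If those who tolerated ACT badly are removed from it, the comparison can look neutral or favourable while some adolescents got worse. The report would then support a statement about distress in those who finished ACT, not in those assigned to it.

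**Working it through.** **1. Tracing one participant through the stated rules.** Take an ACT participant who is upset by Session 1, skips Session 2 and remains an inpatient.
- Section 2.5 still invites this participant to complete the Time 1 questionnaires in week 3, so a DASS-21 score may well exist.
- Section 2.9 excludes the participant for a missed session and says the data will not be analysed.
- A participant who leaves the programme altogether is excluded by the dropout sentence.

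In both cases the person contributes to neither the DASS-21 nor the DERS comparison. A TAU participant who becomes equally distressed but stays in hospital and completes the forms is analysed. This reads therapy session as an ACT session. If weekly TAU counselling counts as well, both arms can lose participants, but the ACT arm still has three more sessions to miss.

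**2. The planned sample size.** Inputs from Section 2.8: f = 0.2, alpha 0.05, power 0.95, correlation 0.3, two groups, two times, non-sphericity 1.
- Noncentrality = f² × N × 2 / (1 − 0.3). At N = 116 this is 0.04 × 116 × 2 / 0.7 = 13.26.
- With 1 and 114 degrees of freedom, power is 0.9506. The smallest even N reaching 0.95 is 116, so the stated 58 per group is reproduced.

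The abstract gives 50 participants, about 25 per arm. That conflict is a separate matter, so both sizes are used below.

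**3. What remains visible.** For the between-arm t-test at Time 1 (two-sided 0.05), 80% power is reached at d = 0.53 with 58 per arm and d = 0.81 with 25 per arm, before exclusions reduce these numbers. A mean worsening of that size among completers would be seen.

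**4. What is removed.** Let a share q of the ACT arm leave or skip after worsening by w SD, and let completers change by c on average (positive means worse).
- True ACT mean change = q·w + (1 − q)·c.
- Completer mean change = c.
- Amount missed = q·(w − c).

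The article gives no value for q or w, so these are assumed. With c = 0 the amount missed is q·w:

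| q | w = 0.5 SD | w = 1.0 SD |
|---|---|---|
| 5% | 0.025 SD | 0.05 SD |
| 10% | 0.05 SD | 0.10 SD |
| 20% | 0.10 SD | 0.20 SD |

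If completers improve (c below zero), the amount missed is larger. In persons, 5% to 20% is 2.9 to 11.6 of 58, or 1.25 to 5 of 25. None of them appears in the analysed distress result.

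**5. Reading the size.** The shift in the mean is modest: even 0.20 SD is well below the 0.53 SD detectable in step 3. The greater loss is at the individual level. The planned analyses compare means only, and the people most likely to have worsened are not in them.

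**The case against.** The strongest reply is that distress is measured systematically. DASS-21 and DERS are completed under supervision by both arms at both times, and the planned tests look in both directions. Patients are also inpatients who see a clinical psychologist at least weekly. This stands. A reader might infer that the trial cannot detect harm, or that distress is seen only if the adolescent asks for help. The document does not support either inference, because average worsening among completers would show.

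A second reply is that a condensed article need not describe adverse-event recording. Figure 1 and the Supplementary Materials are not shown, and the full protocol is not at hand. This also stands. A reader might infer that discomfort is never counted by arm, but that would rest on silence. Nor does exclusion from the analysed sample prevent the report from giving dropouts and exclusions by arm. And with no discomfort event defined in the article, there is no zero count to which a confidence bound could be attached.

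Third, Table 1 should not be overread. For Session 1 it says "The purpose of this session is to develop the willingness to experiencing distress and undesirable private events as part of human experience", which concerns willingness towards distress and does not say that the session sets out to cause it.

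None of this answers the exclusion rule itself. It is printed in Section 2.9 as an analysis decision, and it applies to the distress outcomes as much as to the primary outcome.

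**Conclusion.** The point holds as a matter of who is analysed. Under Section 2.9, adolescents who stop ACT because of the discomfort foreseen in Section 2.5 are absent from the DASS-21 and DERS comparisons, so these cover completers only and can understate worsening under ACT.

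The direction assumes that some ACT participants skip or leave because they feel worse. If all losses are unrelated to distress, this particular bias disappears. Under the assumed rates the arm mean is off by 0.025 to 0.20 SD, and all the individual cases among leavers are lost. The conclusion does not extend to saying that harm is undetectable or that discomfort goes unrecorded. The change is worth making because the outcome bears on safety in minors and the remedy is cheap.

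**What to change.** Amend Section 2.9, with a matching line in Section 2.5:

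- Collect the Time 1 DASS-21 from every randomised participant still reachable, including those who stopped sessions. Section 2.5 already invites both arms, so for those still in hospital this mainly means stating that stopping sessions does not end data collection.
- Analyse and report it by randomised arm without the Section 2.9 exclusions, and do the same for the DERS where available. A completer analysis can stay as a supplementary result.
- Report by arm the number whose DASS-21 worsens by more than a pre-specified threshold that exceeds measurement error. As an illustration, the total-score alpha of 0.92 in Section 2.3.2 gives 1.96 × √2 × √(1 − 0.92) = 0.78 baseline SD. Alpha does not capture fluctuation over time, so this is a lower guide.
- Report by arm the numbers of withdrawals, missed sessions and exclusions with reasons, including any discomfort consultations.

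The cost is slightly more follow-up and one descriptive table, with no extra patients or scheduled visits. Some of the reported worsening will be unrelated to ACT. Showing both arms side by side lets the reader judge that.

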### 2.6. The ACT-Based Intervention

Participants assigned to the ACT group will attend treatment as usual plus a brief ACT-based intervention comprising three sessions, provided once a week, lasting about one hour each. The proposed intervention was designed by the authors of the study. It was developed following the main ACT-based manuals with adjustments according to the users and the context of the study implementation [54,55,56]. The ACT-based intervention is aimed to promote acceptance, awareness, and engagement in valued behaviors, as alternatives to deal with dysfunctional thoughts and feelings. Experiential exercises and key metaphors will be used to target the core processes of the intervention. 

Specifically, we developed a practical and interactive intervention, which comprises practical activities such as roleplay and writing activities and imaginative activities supported by metaphors. The sessions are based on the use of age-appropriate language to convey the most complex therapeutic processes easily. According to the model of Strosahl and colleagues [57], sessions will respectively target the components of openness, awareness, and engagement. In the Openness session, young patients are guided to recognize distressing thoughts, emotions, or body sensations they are dealing with and imagine what their life would be like without their source of suffering. Then, they are invited to recognize their ineffective strategies they use for controlling or avoid pain instead of working on growing life. In the Awareness section, young patients are guided to learn how to feel in contact with the present internal states at the moment they are and just note what they are experiencing, without reacting. They are also invited to consider the self as a viewpoint, or a psychological space from which observing their thoughts and feelings without being overwhelmed. Finally, in the Engagement session, young patients are asked to list the personal qualities they have or those they desire to have for themselves. They are also guided to clarify their values, as chosen life direction they desire to pursue to become the person they want to be. Then, they are required to identify which behaviors need to be engaged in order to achieve their values.

A detailed description of the sessions is provided in Table 1.

### 2.7. Treatment Fidelity 

The research group comprises licensed psychologists, researchers, and doctoral students with expertise in clinical interventions in health care settings and research. 

Sessions will be administered by a licensed clinical psychologist with about three years of expertise in ACT clinical practice for adolescents both in individual and group settings blinded to research aims. 

The structure and the content of the sessions are consistent with ACT theory, as mentioned above. 

To ensure that the intervention will be delivered as planned, direct observation of the intervention is guaranteed. In line with previous studies [59] two independent bachelor-level observers blinded to research aims will observe at least 20% of sessions to evaluate their adherence to the protocol, after a period of training. By using a checklist, they will assess the coverage of the intervention’s components. Checklists include all the contents and the experiential exercises planned for each session. Coders have to achieve a minimum of 80% reliability with the expert trainers and each other. With a lower level of agreement, the data will be dismissed.

### 2.8. Sample Size Calculation

In line with previous studies [60,61] to calculate the sample size, an a priori power analysis was carried out using the software G.Power 3.1.9.4 [62]. 

The required sample size was computed for an analysis of variance (ANOVA) with 2 groups (between variable; ACT + TAU vs. TAU) × 2 times (within variable; Time 0/Time 1). To the best of the author’s knowledge, no other similar studies are available in the literature. Therefore, the a priori effect size (Cohen’s *f*) for the global effect (groups x time) was set to 0.2 (small effect size) [63]. Moreover, the Type I error [α] probability was set to 0.05, and the power [1-β] was set to 0.95. In addition, correlation among repeated measures to 0.3 (small–moderate correlation/linear effect). Non-sphericity was assumed, and it was set to 1. Results showed that there is a more than 95% chance of correctly rejecting the null hypothesis of no significant effect of the interaction with an overall sample of 116 subjects: a minimum of 58 participants per group.

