Several ACT-based protocols have been successfully applied to adolescents targeting a broad range of conditions, such as cystic fibrosis [25], chronic pain [26], ADHD [27], and at-risk adolescents [28]. In a pilot study conducted by Hayes, Boyd, and Sewell [29] thirty adolescents referred to a psychiatric outpatient service were randomly assigned to two conditions: in one, they received an ACT intervention; in the other, participants received a standard intervention for depression. The results showed a significant decrease in depressive symptoms in patients undergoing the ACT intervention. In a study conducted by Kemani and colleagues [30], an ACT-based intervention was applied to adolescents with chronic pain and their family members. Results showed improved acceptance of chronic pain and psychological flexibility in adolescents as well as decreased depressive symptoms in their parents. ACT has also been applied to adolescents with post-traumatic stress disorder [31], proving a reduction of symptoms after a 10-week intervention. 

Unfortunately, there are not many studies in the literature concerning the application of an ACT protocol for adolescents with overweight/obesity problems. However, evidence suggests that psychological flexibility is an important key factor of psychological health, since it allows people to engage in meaningful challenges, following a person’s self-concept and important life domains [22]. To the best of our knowledge, only one pilot study published in 2019 [32], evaluating the effectiveness of an ACT-based psychological intervention applied in combination with a 16-week lifestyle behavioral modification program in a sample of obese adolescents, was found. This study showed that the intervention was effective in promoting a reduction in BMI and an overall improvement in physical activity and psychological status of obese adolescents. Furthermore, the intervention was positively evaluated by both the adolescents and their parents who participated in the study.

Given these premises, the present study aims to evaluate the effectiveness of a brief ACT-based psychological intervention, compared to TAU in improving psychological conditions in a sample of adolescents with obesity attending a multidisciplinary rehabilitation program for weight loss. 

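### The 116 participants give 95% power for a 0.8 SD between-arm difference in change, which the label 'small' in Section 2.8 misdescribes

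*Protocol article*

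**What the plan says.** Section 2.8 (Sample Size Calculation) describes the calculation this way: "The required sample size was computed for an analysis of variance (ANOVA) with 2 groups (between variable; ACT + TAU vs. TAU) × 2 times". It was run in G*Power ("an a priori power analysis was carried out using the software G.Power 3.1.9.4"). The effect size "for the global effect (groups x time) was set to 0.2 (small effect size"), "the Type I error [α] probability was set to 0.05" and "the power [1-β] was set to 0.95". The correlation between the two measurements is set to 0.3 and the non-sphericity value to 1. The result is 116 participants, 58 per group.

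Section 2.9 (Statistical Analysis) gives two sets of benchmarks. For the global effect, f from 0.10 to 0.25 is small, 0.25 to 0.40 moderate and 0.40 or more large. For the focused t-tests, including the comparison of the arms after treatment, the bands for d are "small (d from 0.20 to 0.49), moderate (d from 0.50 to 0.79), and strong" above 0.80. Nowhere is f = 0.2 translated into a difference between the arms.

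**The concern.** A reader of Section 2.8 will understand that the trial has a 95% chance of detecting a small benefit. Whether that is true depends on what f = 0.2 means as a difference between arms. For two independent groups f is d/2, so 0.2 would be d = 0.4. For the interaction in a 2 × 2 repeated-measures design the relation is different, and the same f stands for twice that difference.

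At stake is how a non-significant result is read. If the trial is taken to be powered for small effects, such a result looks like evidence against even a small benefit of three one-hour sessions added to an active inpatient programme.

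**Working it through.** **Inputs.** From Section 2.8: f = 0.2, α = 0.05, power 0.95, correlation ρ = 0.3, 2 groups, m = 2 times, non-sphericity 1 (no effect with two time points). From Section 2.4: 1:1 allocation.

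**Step 1: reproduce 116.** For the group × time interaction, use the noncentral F with 1 and N − 2 degrees of freedom and λ = f²·N·m/(1 − ρ).
- N = 116: λ = 0.04 × 116 × 2/0.7 = 13.257, power 0.9506.
- N = 114: λ = 13.029, power 0.9472.

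So 116 is the smallest even N that reaches 95%. Two other conventions for f do not give it: λ = f²·N needs 328, and λ = f²·(N − 2) needs 330. The protocol's own result therefore shows which f was used.

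**Step 2: translate f.** In this convention f is the SD of the four interaction effects divided by the within-cell SD. A between-arm difference in change of δ gives interaction effects of ±δ/4. Hence f = δ/(4·SD), and δ = 4 × 0.2 = 0.8 SD.

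Check through the t-test on change scores, which is the same test: λ = δ²·N/[8(1 − ρ)·SD²] = 0.64 × 116/(8 × 0.7) = 13.257, as before.

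**Step 3: the same effect on other scales.**
- Arms equal at baseline: a 0.8 SD difference at the post-treatment assessment.
- Change-score SD = √[2(1 − 0.3)] = 1.183 raw SD, so 0.8/1.183 = 0.68 change-score SD.
- f on the partial scale: f² = 0.04 × 2/0.7 = 0.114, f = 0.338, partial η² = 0.114/1.114 = 0.10.
- Classical η² = 0.04/1.04 = 0.038.

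Against Section 2.9, f = 0.2 and classical η² of 0.038 are small. The raw d of 0.80 lies at the boundary of moderate and strong. The d of 0.68 and the partial-scale f of 0.338 are moderate.

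**Step 4: power at N = 116 for other differences.** Power follows from λ = δ²·116/[8(1 − ρ)], two-sided α = 0.05. The 95%-detectable difference is 0.8·√[(1 − ρ)/0.7].

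| ρ | 0.2 SD | 0.3 SD | 0.5 SD | Detectable with 95% power |
|---|---|---|---|---|
| 0.3 | 15% | 27% | 62% | 0.80 SD |
| 0.5 | 19% | 36% | 76% | 0.68 SD |
| 0.7 | 28% | 54% | 93% | 0.52 SD |
| 0.8 | 39% | 72% | 99% | 0.43 SD |

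At ρ = 0.3, power at 0.49 SD, the top of the small d band, is 60%. A simulation with 58 per arm at ρ = 0.3 gave 95.2% at 0.8 SD and 14.6% at 0.2 SD, in agreement.

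The detectable difference equals 0.49 SD when 1 − ρ = 0.7 × (0.49/0.8)² = 0.263, that is ρ ≈ 0.74.

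**The case against.** The strongest reply is that nothing was miscalculated and that the label follows the protocol's own table for this quantity: f = 0.2 lies in the small band of 0.10 to 0.25, while the d bands are assigned to the t-tests. That stands. It is not an arithmetic error, and a reader should not infer one. But the two tables grade the same data differently, and Section 2.9 will grade the post-treatment difference by d. Nor does the f table support 95% power for small effects in general: at f = 0.10 (0.4 SD), power at N = 116 is 44%.

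Three stronger readings are tempting but not supported.

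- *The trial is powered only for a large effect.* On Section 2.9's scales, 0.68 and f = 0.338 are moderate, partial η² of 0.10 is below the 0.110 cut for large, and a d of exactly 0.80 is only the boundary of strong.
- *A higher pre-post correlation cannot rescue the label.* Section 2.3.1 gives retest correlations of 0.78 to 0.82 for four of the six well-being dimensions. At those values the detectable difference is 0.45 to 0.41 SD, inside the small d band. The other two dimensions have 0.21 and 0.31, no value is given for the total score, and the calculation itself uses 0.3. So the dependence on ρ should be shown, not argued away.
- *The reason for using a default effect size is contradicted.* Section 2.8 says that "no other similar studies are available in the literature", while the Introduction cites "only one pilot study published in 2019" in adolescents with obesity. That pilot combined ACT with a 16-week lifestyle programme, whereas this trial tests three sessions in a three-week admission. The word similar can reasonably exclude it, and the article reports no effect size from it.

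It can also be said that nowhere does the article state that a null result would exclude small benefits. That is correct. The misreading is a risk created by the label, not a stated conclusion.

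**Conclusion.** The concern holds as a matter of interpretation. N = 116 is correct for the stated inputs, but the trial is powered for a between-arm difference in change of 0.8 raw SD, which is moderate to borderline strong on the protocol's d scale. Across its small d band (0.20 to 0.49), power is about 15% to 60% at ρ = 0.3, not 95%. If d is expressed in change-score SDs, the range is about 19% to 74%, and the conclusion is the same. Even at ρ = 0.8, power at 0.2 SD is 39%.

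This rests on the effect-size convention that reproduces 116, a common SD at both times, equal arms and 116 analysed participants. The fifty participants named in the Abstract are a separate discrepancy; none of these figures uses that number.

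**What to change.** In Section 2.8, replace the description of the effect as small with a statement such as: *116 analysed participants give 95% power for a between-arm difference in change of 0.8 SD of the outcome, assuming a pre-post correlation of 0.3.* Add power at 0.2, 0.3 and 0.5 SD for correlations from 0.3 to 0.8, as in the table above. State that a non-significant result does not exclude small effects, nor moderate ones unless the correlation is high.

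The cost is wording and a less favourable stated power. The sample size and the analysis do not change.
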